### Aim 3b) Examine safety and efficacy of OMT in caries and periodontal disease model

#### Caries model

Sprague-Dawley rats will be used and screened for the presence of *Streptococcus rattus* (analogous to *Streptococcus mutans)* by polymerase chain reaction. The animals will be fed the NIH diet 2000 [53] containing either 0% sucrose (non-cariogenic) or 56% sucrose (cariogenic), which are fed by program feeding (5 times/day) to reduce artefacts due to eating frequency. The rodents will be intermixed weekly and co-housed for 4 weeks to enable adjustment to the environment and ameliorate their microbiota.

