#### Animals

6–8 weeks old, Sprague-Dawley rats and Balb/c mice will be used in healthy trials of OMT. The animals will be obtained from the Laboratory Animal Services of the University of Adelaide and will be housed in animal holding facilities. All animals will be subjected to 5 days of acclimatization and be housed together to promote amelioration of the microbiota between animals. Animals would be caged in screen-bottomed cages, as this prevents accumulation of faeces and urine in the cage. Bedding for the animals will not be used as the animals might ingest it, which can lead to impaction in fissures and interproximal areas [51]. The animals’ diet will comprise powdered, sterile, non-granular food to prevent impaction of food around the gingiva and they would have access to sterile non-acidic water *ad libitum*. They will be kept in a room with a 12-hr light/dark cycle with temperature ranging from 22 to 24°C [52].

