#### Experimental design

Eight 10-day-old rats from different litters will be evenly distributed amongst four groups and monitored for 4 weeks.

*Control group 1*: no bacteria but fed non-cariogenic diet.*Control group 2*: no bacteria but fed cariogenic diet.*Experimental group 1*: OMT once daily for three days with non-cariogenic diet.*Experimental group 2*: OMT once daily for three days with cariogenic diet.

Before the transplantation of the oral microbiome, full mouth debridement would be done for all the rats in experimental group followed by oral irrigation with 0.1% of sodium hypochlorite. The sodium hypochlorite would be buffered with a neutralising agent [27]. Caries will be scored using a method described by Keyes [54] and Larson [55], which provides information on the lesion sites and severity. After 4 weeks, the rats will be humanely euthanized by carbon dioxide chamber (CO_2_) for 5–7 min. The maxilla and mandible will be harvested by sharp dissection and de-fleshed mechanically. The jaws would be fixed in 10% formalin and 1% sodium hypochlorite solution for a minimum 48 hours before defleshing. Scored jaws will be kept to ensure consistency in scoring between three biological replicates. Microbiota will be assessed at baseline, 1 day post- OMT, and at the end of 4 weeks, as described in Aim 3a.

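### Caries model: 4 weeks of co-housing with weekly mixing cannot come before a start at 10 days of age, so as written it overlaps the experiment and could expose the controls to OMT microbiota

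*Protocol article*

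**What the plan says.** Three places in the protocol article bear on how the caries-model rats are housed and when.

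- Aim 3b, Caries model: "The rodents will be intermixed weekly and co-housed for 4 weeks to enable adjustment to the environment and ameliorate their microbiota".
- Aim 3b, Experimental design: "Eight 10-day-old rats from different litters will be evenly distributed amongst four groups and monitored for 4 weeks". The end is fixed in the same section: "After 4 weeks, the rats will be humanely euthanized by carbon dioxide chamber".
- Aim 3, Animals: "All animals will be subjected to 5 days of acclimatization and be housed together to promote amelioration of the microbiota between animals".

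Two of the four groups receive no bacteria and two receive OMT, one of each on each diet. On the cariogenic diet the contrast is between "no bacteria but fed cariogenic diet" and "OMT once daily for three days with cariogenic diet". The outcomes are caries scores and the microbiota itself: "Microbiota will be assessed at baseline, 1 day post- OMT, and at the end of 4 weeks, as described in Aim 3a". No section says whether cages hold one treatment group only, or when mixing stops relative to allocation or OMT. The end of the Periodontitis model section says that all data are compared by ANOVA with three biological replicates.

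**The concern.** Co-housing to help animals adjust and to act on their microbiota is a sensible run-in. It works against the experiment if it continues after OMT, because the intervention is itself a transferred microbiota and the controls are defined by not receiving it. If OMT and control rats share cages or are reshuffled weekly after treatment, donor organisms may reach the controls. The difference in engraftment and caries would shrink, and the safety comparison would blur. A null result could then mean either that OMT does not work or that the controls were partly treated, and the data could not tell these apart. The question is whether the stated ages and durations leave room for the mixing to be a run-in.

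**Working it through.** **Inputs.** Co-housing with weekly mixing: 4 weeks = 28 days (Caries model). Age at distribution to groups: 10 days; monitoring: 4 weeks = 28 days (Experimental design). Acclimatisation: 5 days (Animals). The protocol gives no sample-size, power or contamination figure for the animal work, so there is no figure of its own to reproduce.

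**Can the mixing finish before allocation?** Required start = 10 − 28 = day −18 of life. It cannot.

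**How much overlaps the experiment?** As written, the experiment runs from day 10 to day 10 + 28 = 38.

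| Mixing starts | Mixing ends | Mixing days inside the experiment | Days left after mixing |
|---|---|---|---|
| At birth (day 0) | day 28 | 28 − 10 = 18 of 28 | 38 − 28 = 10 |
| At allocation (day 10) | day 38 | 28 of 28 | 0 |

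**Could OMT simply wait until mixing ends?** The caries section gives no date for OMT, so overlap with the experiment does not by itself prove overlap with the period after OMT. In the first row, 3 days of OMT would leave 10 − 3 = 7 days of follow-up. In the second row there would be no time for OMT at all. Neither fits the final assessment in Aim 3a, to which the caries section refers and which is made 4 weeks after OMT.

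**Could everything be run in sequence?** Entry at day 10, co-housing to day 10 + 28 = 38, then 4 weeks to day 38 + 28 = 66. This is feasible, but the Experimental design sentence ties the 10-day age to distribution and to the 4 weeks of monitoring. It does not describe rats that start at about 38 days of age.

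**The third figure.** Five days of acclimatisation for all animals could fit before day 10, but it is not the 28 days in the Caries model section.

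**What dilution would do (illustration only).** If cross-transfer removes a fraction c of a true difference δ, the observed difference is δ(1 − c), and the animals needed for the same power rise by 1/(1 − c)². For assumed c = 0.25, 0.50 and 0.75 this gives 1/0.5625 = 1.8, 1/0.25 = 4 and 1/0.0625 = 16 times. The document gives no basis for choosing c.

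**The case against.** The strongest reply is that the mixing was plainly meant as a run-in. It is described as adjustment to the environment and comes before the Experimental design heading, and two diets given by programmed feeding sit badly with cages mixed across groups. The document never says that rats are mixed across treatment groups or after OMT. All of that stands, and it is why spread to the controls is only an inference here. It does not remove the conflict, because a 28-day run-in cannot precede allocation at 10 days of age. Separation by diet would not protect the main contrast either, since the OMT and control rats on the cariogenic diet share a diet.

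It can also be said that an article condenses the full protocol and that caging may be set out there. That is fair for the caging detail, but not for an age, a mixing period and a monitoring period that the article does state and that do not fit together.

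A reader might infer three stronger points that the document does not support:

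- **That power is known to fall by a given amount.** Power worked out at eight animals per group would not describe this model. The text most naturally reads as eight rats over four groups, so 8/4 = 2 per group, or 2 × 3 = 6 over three replicates. Eight per group belongs to the mouse periodontitis model. The effect size and the transfer fraction would also be assumptions.
- **That contamination and too-narrow error bars occur together.** Contamination needs cages that mix groups; inflated type I error needs cages that hold one group. In simulated cages with one animal from each group and assumed intracage correlations of 0.1, 0.3 and 0.5, ANOVA ignoring cage had a type I error of about 4%, 2% and 1%, which is conservative.
- **That Aim 3a and the periodontitis model share the fault.** For them the document states only the 5-day acclimatisation with shared housing, without 4 weeks of weekly mixing or this age conflict.

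**Conclusion.** The concern holds as a conflict of timing with a plausible consequence. The Caries model and Experimental design sections cannot both be followed with the mixing as a run-in: at least 18 of the 28 mixing days, and all 28 if mixing starts at allocation, fall inside the 4-week experiment. This rests only on the document's own ages and durations and on counting the 4 weeks of monitoring from the stated age.

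The possible bias of the OMT-control difference towards zero rests on two further assumptions: that mixing crosses treatment groups, and that it continues after OMT. The document neither states nor excludes them. The direction of the bias follows from the stated purpose of the mixing; its size cannot be computed. The point should be settled before the animal work starts, because contamination of the controls cannot be undone in the analysis.

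**What to change.** 1. Reconcile the co-housing period, the age at entry and the start of the 4-week monitoring across the Animals, Caries model and Experimental design sections, and give the day of the first OMT on the same time axis. Which of the present figures was intended is for the investigators to say.
2. State that mixing across treatment groups ends before the first OMT, and that each animal is afterwards housed only with its own group.
3. Use more than one cage per group across the three replicates, so that cage is not confounded with group.
4. Once cages hold a single group, allow for cage or replicate in the ANOVA, since cage-mates share a microbiota. For example, if each replicate has one cage per group, there are 4 × 3 = 12 cage means. An ANOVA of these with replicate as a block has 11 − 3 − 2 = 6 error degrees of freedom.

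The cost is a few sentences on timing and housing, one term in the model and some extra cages. The analysis in step 4 has few error degrees of freedom, which is better known before the experiment than after it.

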#### Experimental design

Eight 10-day-old rats from different litters will be evenly distributed amongst four groups and monitored for 4 weeks.

*Control group 1*: no bacteria but fed non-cariogenic diet.*Control group 2*: no bacteria but fed cariogenic diet.*Experimental group 1*: OMT once daily for three days with non-cariogenic diet.*Experimental group 2*: OMT once daily for three days with cariogenic diet.

Before the transplantation of the oral microbiome, full mouth debridement would be done for all the rats in experimental group followed by oral irrigation with 0.1% of sodium hypochlorite. The sodium hypochlorite would be buffered with a neutralising agent [27]. Caries will be scored using a method described by Keyes [54] and Larson [55], which provides information on the lesion sites and severity. After 4 weeks, the rats will be humanely euthanized by carbon dioxide chamber (CO_2_) for 5–7 min. The maxilla and mandible will be harvested by sharp dissection and de-fleshed mechanically. The jaws would be fixed in 10% formalin and 1% sodium hypochlorite solution for a minimum 48 hours before defleshing. Scored jaws will be kept to ensure consistency in scoring between three biological replicates. Microbiota will be assessed at baseline, 1 day post- OMT, and at the end of 4 weeks, as described in Aim 3a.

#### Periodontitis model

Experimental periodontitis will be induced in 5–7 week old BALB/c mice after an initial 5 days being fed with either control or experimental diet and receiving kanamycin (1mg/mL) ad libitum for a 7-day period in their drinking water to supress the indigenous oral microbiota [56]. For induction of experimental periodontitis, the mice will be inoculated with either the suspension vehicle only (2% carboxyl-methylcellulose) or *Fusobacterium nucleatum* and *Porphyromonas gingivalis* in the periodontium for 5 weeks twice weekly. The inoculation will consist of 100 μL of bacteria either 10^10^ colony‐forming units/mL of *P*. *gingivalis* alone or 5×10^9^ colony‐forming units/mL of *P*.*gingivalis* and 5×10^9^ colony‐forming units/mL of *F*.*nucleatum* suspended in 2% carboxymethyl cellulose [57]. Experimental mice will receive the OMT one week after *F*.*nucleatum* and *P*.*gingivalis* inoculation. Each group will consist of eight mice from different litters:

*Control group 1*: orally inoculated with the suspension vehicle.*Control group 2*: mice inoculated with *F*.*nucleatum* and *P*.*gingivalis*.*Experimental group 1*: Inoculated with suspension vehicle with OMT once daily for 3 days.*Experimental group 2*: *F*.*nucleatum* and *P*.*gingivalis* inoculation followed by OMT once daily for 3 days.

To reduce the effect of periodontal inflammation all the mice would undergo full mouth scaling and polishing before oral microbiome transplantation on experimental group. To further supress the resident microbiota of the recipient mice, subgingival and oral irrigation with 0.1% sodium hypochlorite would be done for 5 min. The sodium hypochlorite would then be inactivated by using 23μM buffered sodium ascorbate for 10 min [25, 27]. The OMT would be delivered locally in hydrogel loaded dental tray. The loss of alveolar bone will be measured prior to OMTs/infections and throughout the experiment by live animal computed tomography scanner (Skyscan 1076 High Resolution *In Vivo* Scanner; Skyscan, Kontich, Belgium) measuring changes in bone volume from the cemento-enamel junction to the alveolar bone crest in the jaws [58]. The scanner has a 10 megapixel camera with a tungsten 100 kV X-ray source and a spot size of 5 um. For scanning, the X-ray source will be operated at 75 kV X-ray source and 120 mA with a 1-mm tungsten filter. The scanning width would be set to 35 mm with a pixel of 9 um pixels [58].

After 5 weeks, the rats will be humanely euthanized by CO_2_ and the jaws would be dissected to similar procedure described as above for caries model. Alveolar bone loss will be assessed using a Leica MZI6FA stereomicroscope (Leica Microsystems, Wetzlar, Germany) compared to controls [57]. Microbiome will be assessed by microscopy and high-throughput DNA sequencing.

All the data will be compared using ANOVA, and experiments will consist of three biological replicates. For safety of OMT, the presence and absence of discomfort would be measured by monitoring the vital parameters and any adverse reactions of the oral mucosa like redness, inflammation, bleeding, friability of the tissues to the transplants would be recorded separately.

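### At the stated 23 μM, sodium ascorbate cannot inactivate 0.1% sodium hypochlorite at comparable volumes; the unit or concentration needs checking

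*Protocol article*

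**What the plan says.** The Periodontitis model section (Protocol article, Aim 3b) sets out a preparation sequence before oral microbiome transplantation (OMT). After scaling and polishing, a disinfecting rinse is given: "To further supress the resident microbiota of the recipient mice", "subgingival and oral irrigation with 0.1% sodium hypochlorite would be done for 5 min". The next sentence gives the neutraliser, its concentration and its contact time: "The sodium hypochlorite would then be inactivated by using 23μM buffered sodium ascorbate for 10 min". The live donor material follows: "The OMT would be delivered locally in hydrogel loaded dental tray". In the second experimental group the schedule is bacterial "inoculation followed by OMT once daily for 3 days".

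The section does not state the volumes of either solution, a separate rinse, or whether 0.1% is by weight or by volume. The caries model, under its own Experimental design heading, also uses 0.1% hypochlorite but says only "The sodium hypochlorite would be buffered with a neutralising agent", with no agent or concentration. No other part of the article gives an ascorbate concentration.

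For safety, the end of the same section says that "any adverse reactions of the oral mucosa like redness, inflammation, bleeding, friability of the tissues to the transplants would be recorded separately".

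**The concern.** The plan attributes the inactivation to the ascorbate. That is a chemical claim, and it can be checked from the two stated concentrations. One is in the millimolar range and the other is in the tens of micromolar, so the neutraliser looks far too weak for its task.

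This is an operative bench figure in the step just before living bacteria are applied. A laboratory that follows the text would prepare a solution too weak to do what the text says, and nothing in the text would alert it. Residual hypochlorite could act in two ways:

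- It could kill part of the donor microbiota in the first of the three daily doses, which would weaken the apparent effect of OMT.
- It could add its own disinfection or mucosal irritation in the recipient mice. Redness, inflammation, bleeding and friability are to be recorded as reactions to the transplants, so irritation from the rinse could be counted against OMT.

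The article fixes neither the direction nor the size of the net effect. The irrigation is not said to be repeated, so the second and third doses may be unaffected.

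**Working it through.** **Inputs**

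- Hypochlorite: 0.1%, 5 min (Periodontitis model).
- Ascorbate: 23 μM = 0.023 mM, 10 min (Periodontitis model).
- Molar mass of NaOCl: 74.44 g/mol (chemical constant, not in the article).
- Assumed, because not stated: equal volumes; 0.1% as weight per volume (w/v) in the main case; one hypochlorite consumed per ascorbate (ascorbate to dehydroascorbate) in the main case.

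**Main case**

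1. Hypochlorite: 0.1% w/v = 1 g/L; 1 / 74.44 = 0.01343 mol/L = 13.43 mM.
2. Shortfall at 1:1: 13.43 / 0.023 = 584-fold.
3. Fraction neutralised: 0.023 / 13.43 = 0.17%.
4. If one ascorbate consumed three hypochlorite: 13.43 / 3 = 4.48 mM needed; 4.48 / 0.023 = 195-fold short; 3 × 0.023 / 13.43 = 0.51% neutralised.

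The plan's figure is therefore not reproduced as an inactivating concentration.

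**Other readings of 0.1%**

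The shortfall is the hypochlorite concentration divided by (0.023 mM × hypochlorite consumed per ascorbate). The 10:1 column is an extreme bound, full oxidation of ascorbate to carbon dioxide. The stock strengths are assumptions.

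| Reading of 0.1% | Hypochlorite | Shortfall 1:1 | Shortfall 3:1 | Shortfall 10:1 |
|---|---|---|---|---|
| w/v NaOCl: 1 / 74.44 | 13.43 mM | 584 | 195 | 58 |
| As available chlorine: 1 / 70.91 | 14.10 mM | 613 | 204 | 61 |
| v/v of a 12.5% stock: 0.125 / 74.44 | 1.68 mM | 73 | 24 | 7.3 |
| v/v of a 5% stock: 0.05 / 74.44 | 0.67 mM | 29 | 9.7 | 2.9 |

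No cell reaches 1, so 23 μM is insufficient at equal volumes in all of them.

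**What would have to be true for 23 μM to suffice**

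- By volume alone (w/v): about 584 volumes of ascorbate solution per volume of hypochlorite at 1:1, or 195 at 3:1.
- By prior removal (w/v): 1 − 1/584 = 99.8% of the hypochlorite already gone at 1:1, or 1 − 1/195 = 99.5% at 3:1.
- By washout, assuming well-mixed exchange of the mouth volume: ln 584 = 6.4 exchanges at 1:1, or ln 195 = 5.3 at 3:1.
- With v/v of a 5% stock at 3:1: 1 − 1/9.7 = 90% removal, or ln 9.7 = 2.3 exchanges.

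**If the unit were mM**

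23 / 13.43 = 1.71, a 1.7-fold excess at 1:1 and equal volumes.

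**The case against.** The arithmetic is hard to dispute. The best case on the other side concerns consequence and size.

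- **Volumes and flow are not stated.** If the ascorbate were run through a mouse's mouth as an irrigation for 10 minutes, the few exchanges calculated above are plausible, and little hypochlorite might remain. This stands as a limit on the consequence: a harmful residue is not shown. It does not rescue the sentence, because washout or reaction with tissue would then be removing the hypochlorite, not the ascorbate.
- **The basis of 0.1% is open.** Reading it as a dilution by volume of a stock cuts the shortfall to between 29- and 73-fold at 1:1. This stands, and the size should be read as a range. The conclusion does not change.
- **The confounding is partly a separate matter.** If only recipients are irrigated, irrigation is mixed with OMT even under perfect neutralisation, and correcting the unit will not undo that. This is fair. What belongs to the ascorbate figure is only the added effect of a residue, mainly before the first dose.
- **The step is cited to earlier work, and the animal ethics file may carry the right value.** Neither is at hand. The intended value therefore cannot be settled here, but neither possibility alters the stoichiometry of what the article states.
- **It is one reagent unit in a preclinical step.** It does not touch the sample size or the analysis. That limits its weight. It is still a wrong figure in an instruction that a laboratory would follow.

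**Conclusion.** The concern holds: the sentence is wrong as written. At comparable volumes, 23 μM ascorbate falls short of 0.1% w/v hypochlorite by about 584-fold at 1:1 and about 195-fold at 3:1. Across all the readings tried, the shortfall runs from 613-fold down to 2.9-fold, the last needing both the weakest assumed stock and the extreme 10:1 stoichiometry.

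The conclusion rests on comparable volumes and covers only chemical inactivation by the ascorbate, which is what the plan asserts. The residue at the time of OMT, and any effect on results, cannot be determined from the article. A slip of μM for mM is a plausible explanation but is not confirmed. The point should be corrected before the mouse work begins.

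**What to change.** Check the ascorbate unit and concentration in the Periodontitis model section against the working laboratory procedure, and correct it to a value that suffices by molar count. At equal volumes and 0.1% w/v that is at least about 13.4 mM at 1:1, or about 4.5 mM if 3:1 stoichiometry can be justified. If 23 mM was intended, it meets the stricter requirement. Stating the basis of 0.1% and the two volumes alongside would let a reader confirm that the chosen concentration is enough.

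The cost is one corrected figure in the protocol, and in the animal ethics file if the same value appears there. It should be done before any animal is treated.

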## Discussion

To the best of our knowledge, OMT for the treatment and prevention of oral diseases has not been established anywhere in the world. OMT therapy may provide alternative tool to overcome poly-microbial oral diseases that are typically recalcitrant to treatment or prevention such as dental caries and periodontal disease. Our approach represents several strategic advantages at each step.

First, the identification and use of “super donors” in OMT therapy is likely to be a key component for successful OMT. To identify potential “super donors” for OMT, donors must undergo a rigorous selection process. As proposed in our protocol, our proposed screening process involves collecting a detailed medical history and analysis of the microbiome. Any participant under any medication for systemic illness, undergoing treatment, or taking drugs that might have an effect on the immune or inflammatory mechanism would be excluded. This could lead to rejection of high number of participants as observed by many studies [59]. The microbiota from a potential ‘super donor’ will be placed in a biome bank and would be brought to clinical use when needed. Using ‘super donors’ in OMT development should reduce costs, as large number of samples can be stored and processes standardised for safety, traceability, and monitoring. A search for an OMT ‘super donor’ also have further benefits for the oral microbiome research community. Our study will provide the baseline data of composition and characteristics of healthy oral microbiome among Australian adults. Through our questionnaire we are recording many intrinsic host-related factor that are known to affect the oral microbiome, such as diet, physical exercise, oral hygiene habits, access to dental care, socio-economic status and history of smoking and alcohol consumption [60]. We are measuring the buffering capacity of the saliva of each donor and this would help us understand if there is any correlation between species of the oral microflora and favourable pH (6.75–7.25) of the oral cavity [60]. High-throughput DNA sequencing approaches will describe the composition, species, and functions of an oral healthy microbiome among Australians and correlate with genetic background of the donor. Several researchers have examined the healthy oral microbiome only in the context of disease, with little exploration into the function and species that are demonstrative of protective and beneficial oral microbiome [4, 6, 7, 61].

Second, the use of *in vitro* flow cell model is advantageous for several reasons: 1) large amounts of microbiota from a single donor could be mass-produced; 2) biofilms can be screened for pathogens or potentially unwanted species prior to administration; and 3) microbial communities can be manipulated *in vitro* to improve efficacy (*e*.*g*., adding probiotics or removing certain problematic species). Further, an effective *in vitro* growth system of dental plaque also provides opportunities to test biofilm removal and competition, which is critical to examine if or how a recipient’s microbiota may need to be pre-treated before receiving an OMT (i.e., pre-treatment via physical or chemical removal, such as antibiotics). Lastly, this *in vitro* growth strategy could also potentially be adapted to examine unique oral environments. For example, we used 25% mucin rich ASM to mimic a healthy mouth and cultivate a wide range of bacterial species, but serum, sucrose, or other metabolites could be added to mimic unique human diets and lifestyles and examine growth in specific oral environments. For future research, the *in vitro* model would allow us to genetically engineer the biofilm to selectively grow healthy species for transplantation.

Third, adhesive hydrogels are used to administer donor microbiota during OMTs. Adhesive hydrogels have been utilized in humans (e.g. local drug delivery for periodontal therapy and caries prevention [62, 63]), are non-toxic, and can be applied in the mouth for extended periods without irritation (e.g., overnight to 8 days) [64] representing a plausible delivery vehicle for donor microbiota during OMT. Previous research has shown that gram-positive and gram-negative bacterial cells can successfully adhere to hydrogel matrix by cross-linking to the hydrogel polymer chain [65–67]. Hydrogels could prove beneficial for OMT delivery because the hydrogel matrix mimics the extracellular polymer produced in a biofilm [65]. A variety of hydrogels has been used as a carrier material for local drug delivery for bioactive substances for the treatment of periodontitis and dental caries [62, 63, 68, 69]. Hydrogels have multifunctional properties such as structural integrity, slow and controlled release effect, pH- responsiveness, broad antimicrobial spectrum, tissue repair and adhesive properties [68]. Hydrogels can be easily processed into various shapes, especially the injectable and thermos-sensitive hydrogels are capable of filling up narrow spaces in the oral cavity such as gingival crevices and this would be suitable for the delivery of the oral microbiota [64, 69]. For example, hydrogels inoculated with donor microbiota could be easily applied either in a clinical setting or at home by placing the hydrogel in a dental tray, similar to at-home tooth whitening kits that are commercially available today, providing easy ways for application. The hydrogels loaded with oral microbiota could be seeded into a dental tray to deliver and maintain the hydrogel in the subgingival and peri-gingival area, providing a sustained opportunity to seed the microorganisms onto the surface of teeth to endure and overcome the existing selective pressures from the environment of the recipient’s oral cavity [70, 71]. This approach provides a novel means to allow microbiota to be applied topically for a sustained period, which may be critical to achieve a sustained therapeutic effect.

Lastly, this approach utilized murine models to examine OMT safety and efficacy before proceeding with human trials; we selected murine models of oral disease that utilized microbes for disease initiation to ideally represent more natural disease states with dysbiosed microbiota. These experimental models for periodontitis and dental caries in rats and mouse have been very beneficial to our understanding of oral disease progression, providing reproducible radiographic, clinical, molecular and histologic features of human oral disease [51, 57]. Specifically, the bacterially induced experimental periodontitis model (oral gavage model) is important for the study the disease progression and host immune response and would be more suitable for the investigation of the pathophysiological factors induced by oral microorganism’s dysbiosis. Repeated dual inoculation with *P*.*gingivalis* and *F*.*nucleatum* has previously shown to induce alveolar bone loss in an experimental periodontitis model [52, 57]. Alternative models of disease (i.e., silk-ligature models of periodontal disease [72]) could also be examined in the context of OMT efficacy and safety, perhaps providing unique insights into how shifts in immune response during OMT may be linked to health. However, examining if donor OMT can overcome known microorganisms linked to disease may improve our understanding of OMT efficacy in humans.

OMT therapy can be beneficial for the treatment of oral disease and has potential to cause a lifelong shift towards a healthy oral microbiome. Vertical transmission of bacteria has been found between mother and child and occurrence of similar periodontal and cariogenic pathogen [7, 73]. By introducing the therapy in the oral cavity at a younger age, they can benefit by overcoming the “unhealthy” microbiome that might be inherited from their parents. The application of OMT therapy during eruption of the permanent dentition may provide a positive change to person’s oral microbiota for years afterward. In addition, the aging population has increasing levels of dental caries, and OMT applications with the introduction of dental prosthetics could alter the microbiome to a more stable and balanced microbiota. In Australia, the prevalence of moderate and severe periodontitis is also increasing [23, 74]. Current treatment regimens are not successful in completely arresting the disease [75]. OMT therapy could be a potential solution to this problem. OMT could be applied to people at the early stages of disease to stop the progression of disease by creating an environment for the healthy microbiome to form. Australian remote and rural communities are significantly more affected by dental caries and periodontal disease [23], so OMT therapy may be beneficial for remote and rural communities that have limited access to dentists. This therapy could be administered at a key point in life to result in sustained oral microbiota alteration, limiting the need for expensive and time-consuming annual treatments.

